## 6 STUDY ASSESSMENTS

### 6.1 STUDY ASSESSMENTS

Each participant will undergo the same assessments as part of the research protocol. Women with natural menstrual cycles will undergo one additional assessment; this will comprise a urine test to confirm post-ovulation status during the scanning sessions. A urine testing kit will be provided during the consenting procedure (7-10 days prior to scanning) and urine testing will be performed by the participant at home; optionally they may record the result by digital photograph (e.g. on a personal mobile phone). The participant will be asked to confirm ovulation by notification to the CI prior to attending the scanning day. On the morning of scanning, the participant will have the option of showing the CI photographic evidence of the urine test result. The test result will be viewed and recorded by the CI but no photographic images will be transferred or stored.

Each participant will undergo three (approximately 45-minute) brain scanning sessions in a 3T MRI scanner at the Edinburgh Imaging (Royal Infirmary of Edinburgh) Facility on their scheduled scan date (in the morning, afternoon, and late evening). Just prior to their first scheduled scan, each participant will have their actigraphy wristband removed, and their height and weight measured to calculate their body mass index (BMI). They will then be asked to complete an MRI safety checklist before their oral temperature is measured by digital thermometer. The MRI safety checklist and oral temperature measurement will be repeated prior to the second and third scans of the day. During each scan, the whole brain will be imaged to check for any structural abnormalities and to provide structural information to aid localisation and interpretation of  $T_{Br}$  data. MRS scanning will then be performed in superficial and deep regions of the brain in order to obtain data that can be used to estimate brain temperature.

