### *Thermal resilience of the clock is mechanistically elusive*

The phase of mammalian circadian oscillations is highly sensitive to temperature shift, whilst circadian period (clock speed) remains constant across physiological temperatures. This 'temperature compensation' of periodicity comprises a hallmark feature of *bona fide* circadian rhythms, and is poorly understood at the molecular level. Failure of this mechanism may dictate the loss of neural cellular timekeeping in neurodegenerative disease. Thermoregulatory capacity declines with age; suboptimal thermal control could contribute to — and arise from — neural clock dysfunction. Brain temperature ( $T_{Br}$ ) generally exceeds core body temperature ( $T_{Bo}$ ), however, despite the importance of  $T_{Br}$  to neural health, a basic understanding of human  $T_{Br}$  fluctuation is missing.  $T_{Br}$  is difficult to measure and varies by brain region, with neural activity, state of consciousness, and pathology. Although circadian  $T_{Bo}$  cycles are well recognized in mammals, and have reduced amplitudes in aged humans, no studies have examined how human  $T_{Br}$  varies across circadian time. To extract the relevance of thermal-clock interactions to brain health, the molecular clockwork must be studied at physiological human brain temperatures.

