## 1.2 RATIONALE FOR STUDY

Circadian ('around 24 hour') rhythms orchestrate many biological functions and are driven by molecular clocks that exist in every cell - including cells of the brain. These biological clocks are essential for optimal brain health and the regulation of  $T_{Bo}$ . Emerging evidence suggests that brain cell clocks are disrupted in neurodegenerative diseases such as Alzheimer's disease. The risk of these diseases is highest in elderly individuals, who are notoriously poor at regulating their own temperature. In healthy brain cells, molecular clocks maintain circadian rhythms at constant speed, despite temperature fluctuation. Cold-inducible chaperone (CIC) proteins interact with cellular clocks and are highly sensitive to temperature change. We propose that CICs are critical to clock fidelity under  $T_{Br}$  fluctuation, and that failure of this mechanism advances neurodegeneration. First, we must determine how human  $T_{Br}$  varies with time; this represents a fundamental knowledge gap.

$T_{Br}$  fluctuation is reported in rodents, but circadian effects may be confounded by the sleep-wake cycle.  $T_{Br}$  also depends on cerebral haemodynamics, and given species-specific variation in cerebral circulation, extrapolating animal data to humans is problematic. The current gold standard technique for human  $T_{Br}$  measurement requires an intracranial probe, retrieving data from a focal point in the brain parenchyma. This is reserved for patients undergoing neurosurgery, or those with traumatic brain injury. With MRS, high-resolution  $T_{Br}$  data can now be obtained non-invasively in healthy subjects. Pre-existing round-the-clock  $T_{Br}$  data from brain-injured patients has informed the design of an MRS study in human volunteers, to measure healthy  $T_{Br}$  at different times of the day. Derived maximum and minimum  $T_{Br}$  will be used to explore how CICs are involved in the resilience of clocks to physiological temperature shifts using human stem cell-derived brain cells in the lab, potentially leading to novel therapeutic targets for chronic brain disorders.

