### Study procedure

Each participant will be scheduled to attend for three brain scans (approximate duration 45 minutes) at specific times on a single day (morning, afternoon, and late evening) using a 3 Tesla MRI scanner located in a temperature-controlled room at the Edinburgh Imaging (Royal Infirmary of Edinburgh) Facility. After consent is obtained, all participants will wear an actigraphy wristband for one week prior to scanning to establish their normal rest/activity, skin temperature, and light exposure patterns (and therefore their individual chronotype). On arrival at the imaging facility on their scanning day, each participant will have their height and weight recorded, and their actigraphy wristband will be removed and the data downloaded. Prior to each scan, the participant will be asked to change into hospital clothing and to complete an MRI safety and quality checklist (i.e. no metallic/cochlear implants, no metallic jewellery, no makeup that might create imaging artefacts). The participant's temperature will then be measured with an oral thermometer and if the temperature lies above or below the normal oral temperature range (33.2–38.1 °C for women; 35.7–37.7 °C for men), the participant will be rescheduled for an alternative day and any scans already performed on that participant will be excluded from the analysis. For female participants with natural menstrual cycles, a commercially-available urine testing kit (Clearblue) will be provided to confirm ovulation 7-10 days prior to their scheduled scanning date (several test strips supplied during the consenting interview so that urine can be tested for a luteinizing hormone surge on 3 consecutive days if necessary). Should ovulation not be confirmed, further test strips will be provided and the scans rescheduled for the following month. Kits will not be required for women taking monophasic contraception. No urine samples will be collected or stored from any participant; women using the kits must confirm ovulation by notification to the CI ahead of the planned scanning date, and will have the option of bringing a digital photo of the test result with them on the morning of scanning. The result will be viewed by the CI but no photos will be transferred or stored.

For each scan, the protocol will start with structural imaging of the whole brain using standard structural MRI sequences. The MRS protocol will immediately follow the

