structural scan and will consist of acquiring a 1cm thick section of MRS data near the brain surface, and MRS data from another region situated more deeply (including the hypothalamus). The participant will be given written guidance on which activities and consumable products are permissible in between scans and at what time. Meal times will be fixed on the day of scanning to 6am to 8am, 12noon to 2pm, and 6pm to 8pm. Caffeine consumption will be limited to 6am to 8am and 12 noon to 2pm. Participants will be permitted to leave the site between scans but must return 15 minutes prior to their next scheduled scan. If a participant fails to attend their first morning scan (or attends late), they will be invited to reschedule their scanning day once. Participants will be advised that if they attend late to their afternoon or evening scans, these cannot proceed, since the data would be invalid. Participants will be asked to inform the CI via email of any adverse events in the 7 days post-scanning.

All structural scans will be reviewed by a neuroradiologist to check for any abnormalities. All relevant HRFs will be confidentially reported to the participant and their respective GP, adhering to Edinburgh Imaging CRFSOP 19.02 BRIC v03 Radiological Reporting of Research Scans. The neuroradiologist will inform the CI whether or not a participant's data is suitable for inclusion in the analysis (but the CI will not be given any specific information about reasons for exclusion). Only MRS data from structurally-normal brains will be included for analysis.

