## 7 DATA COLLECTION

*Details of observational components of the research methodology and how these will be carried out:*

- Time points for data collection will be specified for each participant in the morning, afternoon, and late evening on their designated day of scanning. BMI will only be measured once immediately prior to the first scan.
- Body weight, height, and oral temperature measurements will be collected by the CI; structural and MRS brain scanning data will be collected by the attending radiographer

- Standardised tools will include wristband-based actigraphy in the 7 days preceding scanning, BMI calculation from body weight and height measurements, oral temperature measurements via digital thermometer, urine testing for ovulation checks (where applicable), structural brain analysis via MRI,  $T_{Br}$  estimation via MRS.
- Methods to maximise completeness of data collection will involve the CI sending an email reminder to each participant 24 hours before scanning. Participants who fail to attend for their first morning scan will be emailed to reschedule their scanning day (there will be one opportunity to reschedule for failed attendance)

Participant rest/activity, skin temperature, and light exposure patterns will be monitored non-invasively over a minimum of 5 days prior to scanning using an actigraphy wristband.

Oral temperature will be measured by the CI immediately prior to subject positioning on the scanner using a precalibrated digital thermometer covered in a disposable one-use thermometer sleeve. The thermometer will be positioned under the tongue with the mouth closed and held in place for 40 seconds. Date, time and temperature will be recorded. Scanning will proceed only if the temperature is within the normal range.

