Urine testing will only be necessary for naturally cycling women recruited into the study. The CI will have prior knowledge of which women require urine testing and a urine testing kit will be provided during the consenting procedure. Participants that require urine testing will be asked to perform the test as directed in the manufacturer's instructions and then take a note of the result together with the date and time it was obtained (optionally they can take a digital photograph of the result using a mobile phone or alternative). They must notify the CI of the result prior to the scanning day so that confirmation of a luteal surge can be recorded by the CI in the Source Data. Participants have the option of bringing a photographic image of the result on the morning of scanning but no images will be transferred or stored.

At each scanning time point the scanning protocol will consist of whole-brain T1- and T2-weighted structural acquisition followed by MRS acquisition in a superficial brain region then a deep brain region. Protocols for data extraction and temperature estimation are established (see Thrippleton *et al.* *NMR Biomed* (2014)). Spectroscopic acquisition from the deep brain region will include the hypothalamus (which contains the suprachiasmatic nucleus where the 'master clock' is situated), and the procedure will be optimized through a pilot scan at Edinburgh Imaging. Scanning will be performed using a PRISMA 3-T clinical MRI scanner (Siemens AG, Healthcare Sector, Erlangen, Germany). MRS  $T_{Br}$  data will be obtained using sequences optimized for each brain region. All images and MRS data will be analysed offline using validated methods (see References).

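### The protocol names sleep/wake state as an influence on brain temperature, but neither asks participants to stay awake in the scanner nor records whether they did

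*Protocol*

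**What the plan says.** **Sleep/wake state as an influence.** Section 1.1 says brain temperature "varies by brain region, with neural activity, state of consciousness, and pathology". Section 1.2 gives as a limit of the rodent evidence that "circadian effects may be confounded by the sleep-wake cycle". Section 3, in its reasoning for the design, says brain temperature depends strongly on the sleep/wake cycle and gives this as a reason for excluding people with known sleep disorders.

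**The measurement.** Section 6.1: "Each participant will undergo three (approximately 45-minute) brain scanning sessions in a 3T MRI scanner", in the morning, afternoon and late evening. The order within a session is fixed in section 7: "structural acquisition followed by MRS acquisition in a superficial brain region then a deep brain region". Oral temperature is taken immediately before the participant is positioned on the scanner (section 7).

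**Sleep-related provisions.** These are the exclusion of known sleep disorders (sections 3 and 4.3), scan times meant not to disturb sleep patterns (section 3), and "wristband-based actigraphy in the 7 days preceding scanning" (section 7) to establish chronotype. On the scanning day the monitor comes off: "Just prior to their first scheduled scan, each participant will have their actigraphy wristband removed" (section 6.1). Between scans, "Participants will be permitted to leave the site between scans but must return 15 minutes prior to their next scheduled scan" (section 3), with written guidance on permitted activities.

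**What is recorded and modelled.** Neither the source data list (section 7.1) nor the participant data form (section 7.2) has an item for wakefulness. The independent variables in section 8.2 are time of day, sex, BMI, chronotype, menstrual phase, brain region and scan duration.

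**The concern.** The primary endpoint is a change in mean brain temperature between time points within the same person. Using each participant as their own control removes stable differences between people. It does not remove a state that can differ between one person's three scans. Chronotype adjustment does not remove it either, because chronotype describes habitual timing and not whether someone was awake during a given acquisition.

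The protocol therefore identifies a confounder of circadian effects, controls for it at recruitment and in scheduling, and leaves it open at the moment of measurement. If sleep in the scanner is more common at one time point than another, the time-of-day estimate mixes the two. The brain-versus-oral comparison is exposed too: the oral reading is taken before positioning, while the brain reading comes after a period of lying still, so sleep in the scanner would affect only the brain value.

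This is a matter of procedure and data collection and cannot be left to a statistical analysis plan. No later model can adjust for a variable that was never recorded.

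**Working it through.** **1. Search for any control of wakefulness during acquisition.**

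| Place in protocol | Provision | Covers wake state during spectroscopy? |
|---|---|---|
| Sections 3, 4.3 | Known sleep disorders excluded | No |
| Section 3 | Scan times chosen to spare sleep patterns | No |
| Sections 3, 7 | Actigraphy before the scanning day | No |
| Section 3 | Written guidance for the time between scans | No |
| Section 6.1 | Safety checklist and oral temperature before each scan | No |
| Sections 7.1, 7.2 | Source data and data form items | No item |
| Section 8.2 | Independent variables | No item |

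**2. The plan's own figure.** Section 8.1 gives 36 subjects, a 0.5 °C difference, 80% power and 5% significance. It states no SD, so 36 cannot be reproduced directly. Solving for the SD of the within-person difference that makes it true, assuming a two-sided pairwise comparison:

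- Normal approximation: 0.5 × √36 / (1.960 + 0.842) = 3.0 / 2.802 = 1.07 °C.
- Paired t-test (noncentral t): 1.04 °C.

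The sample size is not disputed. The 1.04 °C is used only to put the bias on a scale.

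**3. Size of the bias.** Bias in a contrast between two sessions = (share asleep at one minus share asleep at the other) × (shift in brain temperature when asleep). The documents give neither input, so both are assumptions.

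- Low: 0.25 × 0.2 °C = 0.05 °C; 0.05 / 0.5 = 10% of the target.
- High: 0.50 × 0.3 °C = 0.15 °C; 0.15 / 0.5 = 30% of the target.

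**4. What that does to a pairwise paired t-test** (n = 36, SD of difference 1.04 °C, noncentrality = shift × √36 / 1.04):

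| Bias | Rejection rate with no true time effect | Power if the bias opposes a true 0.5 °C |
|---|---|---|
| 0 | 5.0% | 80% |
| 0.05 °C | 5.9% | 71.3% |
| 0.15 °C | 13.4% | 50.1% |

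If the SD of the difference were 0.5 °C instead, the rejection rates with no true effect would be 9.0% at 0.05 °C and 41.7% at 0.15 °C. These figures ignore any extra variance from a mix of sleeping and waking participants.

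**5. Upper limit.** For sleep alone to produce the full 0.5 °C, the product in step 3 must equal 0.5. For example, everyone would be asleep at one session, nobody at the other, with a sleep effect of 0.5 °C.

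**The case against.** **The assumptions carry the number.** The protocol gives neither the size of any sleep effect nor how often people fall asleep in the scanner. It does not say that drowsiness is commoner in the late evening; that is plausible but is an inference. If dozing were equally common at all three sessions, the bias would largely cancel within person. This stands, and the point is conditional for that reason.

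**The direction is open.** The documents shown do not say which session is expected to be warmest in healthy volunteers. Cooling during sleep could create a difference or hide one. This also stands.

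**An instruction may exist elsewhere.** The Participant Information Sheet, the between-scan guidance and the imaging procedures are not shown, and one of them may tell participants to stay awake. That limits what can be said about control. It does not supply the missing record, since the protocol lists what is recorded and wakefulness is not there.

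**There is an indirect check.** Oral temperature is measured at each session before any sleep in the scanner and gives a partial comparison series. It helps interpretation but does not show who slept.

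**The wristband.** A reader might infer that taking it off before the first scan is the fault. The documents do not support that. Its stated purpose is chronotype from the days before scanning, and removal on arrival fits that purpose: "their actigraphy wristband will be removed and the data downloaded". Re-fitting it between scans would not record sleep inside the scanner. Activity between scans is already partly covered by the written guidance, the exclusion for excessive activity and the recording of deviations.

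**Conclusion.** The point holds in conditional form. By the protocol's own account, wake state affects brain temperature and can confound circadian effects, yet it is neither set nor recorded when brain temperature is measured. If it differs between sessions, the primary contrast and the brain-versus-oral comparison could be biased in either direction, with no means of adjustment.

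The size is unknown. Under the stated assumptions the bias is 0.05 to 0.15 °C, or 10% to 30% of the 0.5 °C target. With the back-solved SD of 1.04 °C, pairwise type I error would rise from 5% to between 5.9% and 13.4%. It could be smaller than this or absent.

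A reader might go further and infer that evening sleep will be mistaken for a diurnal change, or that a significant result could not be attributed to time of day. The documents support neither. Clustering of sleep in the evening is not documented, and sleep would explain a full 0.5 °C shift only under extreme values. The change is still worth making: the gap is cheap to close beforehand and cannot be closed afterwards.

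**What to change.** In sections 6.1 and 7:

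- Instruct participants to stay awake during each scan.
- Have the attending radiographer check by intercom between acquisitions, immediately before and after each spectroscopy block.
- Record awake or asleep for each block (superficial and deep) on the Appointment Checklist, with any self-reported nap between scans. A record per block is needed because the deep region always comes last, so sleep setting in during a session would fall more on that region.
- State that a block marked asleep is not non-compliance. Section 8.2 makes a participant's entire data set unusable for non-compliance with the protocol, and a stay-awake instruction could otherwise trigger that rule.

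In section 8.2 or the analysis plan, pre-specify a sensitivity analysis of the primary endpoint without acquisitions marked asleep. The planned mixed model already accepts participants with fewer than three scans, so no new method is needed.

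The wristband schedule need not change.

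Cost: a few seconds of contact per scan and a few checklist entries, with no added visits or equipment. Downsides: a prompt may cause slight movement, which is why it belongs between acquisitions. It may also rouse someone who is dozing, and a brief sleep within an acquisition can still be missed.

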## 7 DATA COLLECTION

*Details of observational components of the research methodology and how these will be carried out:*

- Time points for data collection will be specified for each participant in the morning, afternoon, and late evening on their designated day of scanning. BMI will only be measured once immediately prior to the first scan.
- Body weight, height, and oral temperature measurements will be collected by the CI; structural and MRS brain scanning data will be collected by the attending radiographer

- Standardised tools will include wristband-based actigraphy in the 7 days preceding scanning, BMI calculation from body weight and height measurements, oral temperature measurements via digital thermometer, urine testing for ovulation checks (where applicable), structural brain analysis via MRI,  $T_{Br}$  estimation via MRS.
- Methods to maximise completeness of data collection will involve the CI sending an email reminder to each participant 24 hours before scanning. Participants who fail to attend for their first morning scan will be emailed to reschedule their scanning day (there will be one opportunity to reschedule for failed attendance)

Participant rest/activity, skin temperature, and light exposure patterns will be monitored non-invasively over a minimum of 5 days prior to scanning using an actigraphy wristband.

Oral temperature will be measured by the CI immediately prior to subject positioning on the scanner using a precalibrated digital thermometer covered in a disposable one-use thermometer sleeve. The thermometer will be positioned under the tongue with the mouth closed and held in place for 40 seconds. Date, time and temperature will be recorded. Scanning will proceed only if the temperature is within the normal range.

Urine testing will only be necessary for naturally cycling women recruited into the study. The CI will have prior knowledge of which women require urine testing and a urine testing kit will be provided during the consenting procedure. Participants that require urine testing will be asked to perform the test as directed in the manufacturer's instructions and then take a note of the result together with the date and time it was obtained (optionally they can take a digital photograph of the result using a mobile phone or alternative). They must notify the CI of the result prior to the scanning day so that confirmation of a luteal surge can be recorded by the CI in the Source Data. Participants have the option of bringing a photographic image of the result on the morning of scanning but no images will be transferred or stored.

At each scanning time point the scanning protocol will consist of whole-brain T1- and T2-weighted structural acquisition followed by MRS acquisition in a superficial brain region then a deep brain region. Protocols for data extraction and temperature estimation are established (see Thrippleton *et al.* *NMR Biomed* (2014)). Spectroscopic acquisition from the deep brain region will include the hypothalamus (which contains the suprachiasmatic nucleus where the 'master clock' is situated), and the procedure will be optimized through a pilot scan at Edinburgh Imaging. Scanning will be performed using a PRISMA 3-T clinical MRI scanner (Siemens AG, Healthcare Sector, Erlangen, Germany). MRS  $T_{Br}$  data will be obtained using sequences optimized for each brain region. All images and MRS data will be analysed offline using validated methods (see References).

